## Trial Duration/Schedule

The trial will run over a three-year period, with recruitment commencing in early 2024. Each participant will provide informed consent, after which they will complete a baseline assessment. On completion of the baseline assessments, participants will be randomised to either the experimental or control group and complete a 16-week intervention phase. Thereafter, all participants will complete a suite of re-assessments, (i) mid-way through the intervention phase, (ii) on completion of the intervention phase and, (iii) 12 months following randomisation.

| Milestones                                                           | Timeline        |
|----------------------------------------------------------------------|-----------------|
| 1. Recruit study personnel                                           | July 2023       |
| 2. Complete draft study proposal                                     | November 2023   |
| 3. Submit to ethics/governance                                       | November 2023   |
| 4. Approval obtained from all relevant HREC / RGO                    | February 2024   |
| 5. Commence recruitment (recruitment target = 15 participants/month) | March 2024      |
| 6. Commence intervention                                             | March 2024      |
| 7. Last participant recruitment                                      | March 2026      |
| 8. Complete intervention                                             | July 2026       |
| 9. Complete post-intervention assessments                            | August 2026     |
| 10. Complete long term follow-up assessments                         | March 2027      |
| 11. Data cleaning, analysis and report writing                       | From March 2026 |
| 12. Final study publications and report complete                     | September 2027  |

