## 9 Data Management, Statistical Analysis and Record Keeping

## Statistics and Interim Analysis

*The primary research questions for this study are:*

- Does the SMART program, compared with usual care, change health-related quality of life (primary outcome) measured 16-weeks and 12-months following randomisation?

AND

- Does the SMART program, compared with usual care, change peripheral muscle strength, muscle mass, exercise tolerance, exercise adherence and chemotherapy completion rates (secondary outcomes) measured 16 weeks following randomisation?

The analyses for this research question will be performed according to the intention to treat principle. For the primary outcome, health-related quality of life, with 4 assessment points, linear models will be used to account for repeated measures with participant ID entered as a random effect. The primary time point of interest will be the end of the intervention phase. Group, time and group by time will be analysed as fixed effects and the baseline measure will be entered as a covariate to adjust for random baseline differences. Between group difference for the dependent outcome of chemotherapy completion (yes/no) will be analysed using logistic regression. Between group differences for the remaining secondary measures (peripheral muscle force-generating capacity, muscle mass, exercise tolerance) will be examined using linear regression with the corresponding baseline measure used as a covariate. Data transformations or alternative models (such as gamma distribution) will be considered if there is poor model fit.

Missing data will be examined and multiple imputations investigated (assuming they are missing at random). Models will be adjusted for covariates, randomisation variables and confounders such as age. Estimates of the effects will be reported with their corresponding 95% confidence intervals.

*The first secondary research question is:*

- Do factors such as adherence, treatment pathway and cancer stage moderate the magnitude of any change in primary or secondary outcomes? (i.e. moderator analysis)

To understand any moderator effects, the listed covariates will be entered into a multivariable model using the outcomes listed above. In addition, adherence will be examined to see if it mediates the relationship with the outcomes, by calculating the indirect through the use of partial coefficients.

*The second secondary research question is:*

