- What is the health care utilisation, absenteeism and presenteeism over the 12 months following randomisation?

This is an exploratory question and data will be described using mean and standard deviation.

*The third secondary research question is:*

- Does performance on tests of peripheral muscle force-generating capacity and exercise tolerance, change with test repetition (i.e. is there a learning effect)?

This will be assessed using one-way repeated measures analysis of variance (ANOVA). That is, for each participant, data collected over consecutive trials (5 attempts for each measure of muscle force and 2 attempts for the 6MWT) compared to explore if there is an effect of test repetition on these outcomes.

*The fourth secondary research question is:*

What is the minimal detectable difference in health-related quality of life and exercise tolerance?

This will be assessed using anchor-based approach via a Receiver Operating Characteristic curve. This curve will determine the optimal operating point to discriminate between participants who rate themselves as changed vs unchanged at the end of the SMART program.

*The fifth secondary research question is:*

Do psychological determinants of behavioural change, such as capability, opportunity, and motivation affect adherence to the SMART program and physical activity maintenance?

This will be assessed using correlations and a Multiple Regression Analysis of the data from psychological determinant measures (COM-B factors, impairment in functioning, intention, self-efficacy, habit, and mood) across all time-points for each participant. Data from the exit interviews will also be analysed using qualitative methods (such as thematic analysis) to explore participants' reasons for engagement (or lack of engagement).

*The sixth secondary research question is:*

Does the SMART program improve mood, and does mood influence adherence to the program and physical activity maintenance?

This will be assessed using correlations between mood data from the PANAS (across all timepoints) and physical activity engagement.

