## **Sample Size**

Sample size calculation has been conducted using the EORTC QLQ BR-30 (continuous data) as the dependent variable. To detect a difference between the experimental and control groups in this outcome of 8 (which has been estimated as the minimal clinically important difference), assuming a standard deviation of 20.52 (based on previously published literature) (Karsten 2022), with an  $\alpha = 0.05$  and  $1-\beta = 0.8$ , we will need to 104 participants in the experimental group and 104 participants in the control group. In order to account for 20% drop-out, we plan to recruit a sample size of 130 participants in each group. This means we aim to recruit 260 participants over 24 months (recruitment rate of 11 per month).

We believe that this recruitment rate is realistic. This is because, we have recently completed an audit of the RPH Breast Clinic (GEKO number 50167). The Data, Digital and Innovation (DDI) group at RPH compiled information from WEBPAS and showed that 993 adults were treated with surgical breast procedures and/or chemotherapy treatment for BC at the RPH Breast Clinic between 01/07/2021 to 30/06/2023. This is equivalent to 41 people per month. This means that our recruitment fraction for this study will be 27%.

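### Secondary questions 5 and 6 name independent-row methods for scores taken up to four times per participant and do not fix the unit of analysis; if visits are pooled, type I error exceeds 5%

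*Protocol*

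**What the plan says.** Protocol Section 9 (Statistics and Interim Analysis) sets out the two analyses.

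- **Fifth secondary question** (do psychological determinants affect adherence and maintenance of activity): "This will be assessed using correlations and a Multiple Regression Analysis of the data from psychological determinant measures". The data are those collected "across all time-points for each participant".
- **Sixth secondary question** (mood): "This will be assessed using correlations between mood data from the PANAS (across all timepoints) and physical activity engagement".

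The timing table in Section 7 (Efficacy assessment) marks COM, WSAS, intention, BTSES, HTQ, SRBAI and PANAS before randomisation and at three later assessments. Section 4 (Trial Duration/Schedule) lists those as "i) mid-way through the intervention phase, (ii) on completion of the intervention phase and, (iii) 12 months following randomisation". Each participant can therefore supply four scores per scale. The same table marks participation in exercise only in the weekly column of the intervention phase.

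Elsewhere Section 9 deals with repeated data openly. For the primary outcome, also measured four times, "linear models will be used to account for repeated measures with participant ID entered as a random effect". For the third secondary question (repeated test attempts) it names a repeated-measures ANOVA. Questions 5 and 6 have no comparable term.

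**The concern.** Scores from one person at several visits are correlated. A correlation or least-squares regression that takes each person-visit as a separate row counts them as separate people. Standard errors are then too small, confidence intervals too narrow and p-values too low.

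In the SMART arm, four visits from 104 to 130 participants give 4 × 104 = 416 to 4 × 130 = 520 rows from at most 130 people. If adherence is one value per person, that value would be copied onto each of the person's rows.

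Section 15 lists the effects of these determinants on adherence and maintenance among the trial's likely most important findings. The scales also yield many scores: six COM components, WSAS, two intention items, BTSES, HTQ, SRBAI and two PANAS affects make about 14. At an inflated error rate per test, some could be reported as determinants of adherence by chance.

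**Working it through.** **1. The plan's own figures.** The protocol gives no sample size, error rate or within-person correlation for questions 5 and 6. The only figure to reproduce is the primary sample size in Section 9 (Sample Size): difference 8, SD 20.52, α = 0.05, power 0.80. Taking α as two-sided:

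n per group = 2 × (1.960 + 0.842)² × 20.52² / 8² ≈ 103.3, rounded up to 104. With 20% drop-out, 104 / 0.8 = 130.

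Both match the protocol. These figures set the number of participants used below.

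**2. Inputs for the pooled case.**

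- m, visits pooled per participant: up to 4 (timing table). Also 3, and 2 because only the mid-way and completion visits fall within or at the end of the weekly exercise collection.
- ρx, within-person correlation of the determinant or mood score: not given. Assumed 0.5, range 0.3 to 0.7.
- ρy, within-person correlation of the exercise outcome: 1 if adherence is one value per person, otherwise assumed as for ρx.

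**3. Formula.** With no true association and visits treated as independent:

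DE = 1 + (m − 1) × ρx × ρy

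type I error = 2 × [1 − Φ(1.96 / √DE)]

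**4. Results.** Simulation used 104, 130 and 208 participants, 5,000 runs each.

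| m | ρx | ρy | DE | 1.96/√DE | Type I error | Simulated |
|---|---|---|---|---|---|---|
| 4 | 0.5 | 1 | 2.50 | 1.240 | 21.5% | 21.5–21.7% |
| 4 | 0.5 | 0.5 | 1.75 | 1.482 | 13.8% | 14.2–14.4% |
| 2 | 0.5 | 0.5 | 1.25 | 1.753 | 8.0% | not run |
| 3 | 0.5 | 1 | 2.00 | 1.386 | 16.6% | 16.7–17.6% |
| 3 | 0.5 | 0.5 | 1.50 | 1.600 | 11.0% | 10.8–11.3% |
| 3 | 0.3 | 0.3 | 1.18 | 1.804 | 7.1% | 6.6–7.7% |
| 4 | 0.7 | 0.7 | 2.47 | 1.247 | 21.2% | 21.2–22.1% |
| 4 | 0.7 | 1 | 3.10 | 1.113 | 26.6% | 26.3–27.8% |

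For three or four pooled visits and correlations of 0.3 to 0.7, the range is about 7% to 27%. If either correlation is 0, DE = 1 and the rate stays at 5%.

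**5. Layouts that respect the participant.** Simulated at 104 participants with four visits:

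- participant means: 5.0–5.2%
- one visit at a time: 4.9–5.3%
- one row per participant with the four visit scores as separate predictors: 5.0–5.2%
- pooled rows with cluster-robust errors by participant (2,000 runs): 4.7–7.0%

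The mixed model itself was not simulated.

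**The case against.** The strongest objection is that the protocol never says person-visits are stacked. Its wording also fits visit-by-visit correlations, participant means, or one row per participant with visit scores as separate predictors, and each keeps about 5% per test. This stands. A reader might infer that the plan prescribes a pooled analysis with false positives at 14% to 22%. The documents do not support that: pooling is the likely reading of a single regression on all-visit data, not a stated one, and the percentages need correlations that the protocol does not supply.

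A second objection is that the scenarios fit the schedule unevenly. Exercise participation is marked only weekly during the intervention, with nothing at baseline or 12 months, so four exercise values aligned with four questionnaires are not clearly available. This also stands: the 14% case fits the schedule poorly, and with two aligned visits the figure is about 8%. The 22% case needs one adherence value repeated on four rows, which the protocol does not describe.

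A third objection is that the error structure of secondary association analyses is often left to an SAP, and the protocol says one will be published. That excuses missing detail. It does not cover the mismatch here, where the protocol names both the data (all time points) and methods that assume independent rows, in a section that handles repeated measures explicitly elsewhere.

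Nor do the alternative readings make the wording adequate. With about 14 scores at four visits, separate predictors would number about 14 × 4 = 56 for 104 to 130 SMART participants. Four separate visit correlations per scale give about 16% to 18% for at least one false positive, which is a multiplicity matter distinct from this point.

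**Conclusion.** The concern holds in conditional form. Questions 5 and 6 name methods that assume independent rows for data from up to four time points, with no participant term and no stated unit of analysis.

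If visits are pooled, type I error exceeds the nominal 5%. The sizes in the table rest on an assumed within-person correlation (0.5, range 0.3 to 0.7) and on how exercise is recorded; none of them is a property of the plan as written. If the team intends visit-by-visit or participant-level analyses, this inflation does not arise per test, but the text does not say so.

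The primary endpoint and the sample size are unaffected. The point matters because the protocol expects these associations to be among its main findings.

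**What to change.** In Section 9, under the fifth and sixth secondary questions, state that the participant is the unit of analysis and how repeated scores enter.

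- **Adherence or maintenance as one value per participant:** use one row per participant, for example a prespecified visit, a participant mean, or visit scores as separate predictors.
- **Exercise as a repeated measure with visits pooled:** use the mixed model that the section already specifies for the primary outcome, with participant ID as random effect and time as fixed effect, plus group if both arms are included.

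Reporting between-person and within-person associations separately would add information but is optional.

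The cost is a wording change to two secondary analyses, with no new data or participants and a model family already in the plan. The downside is wider, correct confidence intervals for these two questions.

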### 3 Trial Aims / Objectives / Hypotheses

For all research questions, the study population refers to adults with newly diagnosed with breast cancer who are undergoing treatment through the Breast Clinic at RPH.

Primary research questions:

- 1) Does the SMART program, compared with usual care, change health-related quality of life (primary outcome) measured 16-weeks and 12-months following randomisation?
- 2) Does the SMART program, compared with usual care, change peripheral muscle strength, muscle mass, exercise tolerance, exercise adherence and chemotherapy completion rates (secondary outcomes) measured 16 weeks following randomisation?

Secondary research questions:

- 1) Do factors such as adherence, treatment pathway and cancer stage moderate the magnitude of any change in primary or secondary outcomes? (i.e. moderator analysis)
- 2) What is the health care utilisation, absenteeism and presenteeism over the 12 months following randomisation? (descriptive analyses only, to guide patient expectations in regarding these outcomes)

- 3) Does performance on tests of peripheral muscle force-generating capacity and exercise tolerance, change with test repetition (i.e. is there a learning effect)? (can be answered by Honours students enrolled in the BSc physiotherapy at Curtin University)
- 4) What is the minimal detectable difference in health-related quality of life and exercise tolerance? (can be answered by Honours students enrolled in the BSc physiotherapy at Curtin University)
- 5) Do psychological determinants of behavioural change, such as capability, opportunity, and motivation affect adherence to the SMART program and physical activity maintenance?
- 6) Does the SMART program improve mood, and does mood influence adherence to the program and physical activity maintenance?

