## Efficacy assessment

Data collection will require two visits to the Physiotherapy Department at RPH. These assessments will be approximately 90 minutes in duration and will be completed pre-randomisation (baseline assessment) and at the end of the intervention phase. All other data collection will be done by extracting information from medical records, during phone conversations with the participants or by emailing out questionnaires through online formats (e.g. REDCap).

Table 1: Timing of outcomes

|                                                          | Pre-randomisation | Each week during the intervention phase | Mid-way through the intervention phase | On completion of the of intervention phase | 12 months following randomisation |
|----------------------------------------------------------|--------------------------|------------------------------------------------|-----------------------------------------------|---------------------------------------------------|------------------------------------------|
| Descriptive data (age, sex etc)                          | X                        |                                                |                                               |                                                   |                                          |
| EORTC QLQ C30 with BR45 (health-related quality of life) | X                        |                                                | X                                             | X                                                 | X                                        |
| EQ-5D-5L                                                 | X                        |                                                | X                                             | X                                                 | X                                        |
| Grip strength                                            | X                        |                                                |                                               | X                                                 |                                          |
| Deltoid, bicep and quads strength                        | X                        |                                                |                                               | X                                                 |                                          |

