| SRBAI                                                    | x                        |                                                | x                                             | x                                                 | x                                        |
| PANAS                                                    | x                        |                                                | x                                             | x                                                 | x                                        |
| Participation in exercise                                |                          | X                                              |                                               |                                                   |                                          |
| Healthcare utilisation                                   |                          | X                                              |                                               |                                                   |                                          |
| iMTA (absenteeism / presenteeism)                        |                          |                                                | X                                             | X                                                 | X                                        |
| Acceptability/ feasibility                               |                          |                                                |                                               | x                                                 |                                          |
| Exit interview                                           |                          |                                                |                                               | x                                                 |                                          |

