**1) What are likely to be the most important findings?**

- The effect of the SMART program on a range of patient centred outcome measures.
- The minimal detectable difference for measures of health-related quality of life and exercise tolerance in this patient population.
- Information regarding optimisation of measures of muscle force and exercise tolerance.
- Descriptive data on absenteeism and presenteeism.
- The effects of individual differences in psychological determinants of behaviour change (COM-B factors, impairment in functioning, intention, self-efficacy, habit, and mood) on physical adherence and maintenance.

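### For adherence, secondary questions 5 and 6 use determinants and mood measured during and after the adherence period with no stated time order, so reverse influence could be reported as an effect

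*Protocol*

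**What the plan says.** Section 3 of the protocol poses secondary question 5 in directional terms: "Do psychological determinants of behavioural change, such as capability, opportunity, and motivation affect adherence to the SMART program and physical activity maintenance". Question 6 asks, among other things, whether mood influences adherence.

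The analysis is in Section 9, Statistics and Interim Analysis. For question 5: "This will be assessed using correlations and a Multiple Regression Analysis of the data from psychological determinant measures", with the determinant data taken as "impairment in functioning, intention, self-efficacy, habit, and mood) across all time-points for each participant". For question 6, PANAS scores from all time points are correlated with physical activity engagement. Neither paragraph states a lag, a restriction to baseline, or any other ordering.

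On timing, Section 4 (Trial Duration/Schedule) says that "participants will be randomised to either the experimental or control group and complete a 16-week intervention phase", with re-assessments "i) mid-way through the intervention phase, (ii) on completion of the intervention phase and, (iii) 12 months following randomisation". The timing table under Efficacy assessment in Section 7 marks COM, WSAS, intention, BTSES, HTQ, SRBAI and PANAS before randomisation and at each of those three re-assessments. The row "Participation in exercise" is marked only in the weekly column of the intervention phase.

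Section 15 lists the result among the likely most important findings: "The effects of individual differences in psychological determinants of behaviour change" on adherence and maintenance.

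**The concern.** A score taken at week 16 or at 12 months cannot have affected exercise in weeks 1-16. Any association between them reflects the influence of adherence on the score, stable differences between people, or both. A mid-way score has the same problem for the half of the period already past.

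Reverse influence is plausible for several of the instruments. The adapted COM items ask how able participants feel to achieve their weekly exercise goals, and a participant who has been meeting those goals may answer more favourably for that reason. SRBAI asks how automatic the behaviour feels, which repetition may change. Habit formation is also named among the behaviour change techniques taught in SMART (Section 4, Intervention/Product Description, item 7).

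At stake is the reading of the result. The question is causal and Section 15 plans to report effects. An analysis that pools scores from before, during and after the adherence period cannot tell a driver of adherence from a result of it.

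**Working it through.** **Step 1: order in time.** Taking mid-way as week 8 (16/2):

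| Determinant or PANAS score | Position relative to adherence in weeks 1-16 |
|---|---|
| Before randomisation | Precedes all of it |
| Mid-way | Follows weeks 1-8, precedes weeks 9-16 |
| Completion | Follows all of it |
| 12 months | Follows all of it |

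One of the four scheduled scores fully precedes adherence, one falls inside the period, and two come after it.

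**Step 2: sample size for the illustration.** The protocol gives no figure for question 5, so I use its completers per arm. That figure reproduces: 2 × (1.960 + 0.842)² × 20.52² / 8² = 103.3, rounded up to 104; and 104 / 0.8 = 130 after 20% drop-out.

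**Step 3: a model with no effect of the determinant on adherence.** All coefficients here are assumptions, not figures from the protocol. Let D0 to D3 be the four determinant scores, A1 and A2 adherence in the two halves of the intervention, and e independent standard normal noise (a separate draw in each line):

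- D0 and A1 are independent, each N(0,1)
- D1 = 0.6·D0 + b·A1 + 0.8·e
- A2 = 0.6·A1 + 0.8·e
- D2 = 0.6·D1 + b·A2 + 0.8·e
- D3 = 0.6·D2 + 0.8·e
- A = (A1 + A2)/2

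The reverse effect is b. The determinant never enters the adherence equations.

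**Step 4: the induced correlation.**

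- Var(A) = (1 + 1 + 2 × 0.6)/4 = 0.8
- Cov(D0, A) = 0
- Cov(D1, A) = 0.8b
- Cov(D2, A) = 0.6 × 0.8b + 0.8b = 1.28b
- Cov(D3, A) = 0.6 × 1.28b = 0.768b
- Covariance of the four-point mean with A = (0.8 + 1.28 + 0.768)b/4 = 0.712b
- Variance of the four-point mean = [4 + 2 × (3 × 0.6 + 2 × 0.36 + 0.216)]/16 + b² × Var(1.96·A1 + 1.6·A2)/16 = 0.592 + 0.635b²

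So r = 0.712b / √[0.8 × (0.592 + 0.635b²)]. At b = 0.2 this is 0.1424/0.703 = 0.203. By Fisher's z with n = 104, atanh(0.203) × √101 = 2.07, which gives a two-sided rejection rate of about 54%.

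**Step 5: simulation of the same model** (n = 104, 1,500 trials per setting, two-sided 5% tests):

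| Reverse effect b (SD) | r, formula | r, simulated | False positives, baseline score | False positives, four-point mean | False positives, all four entered (F test) |
|---|---|---|---|---|---|
| 0 | 0.00 | 0.00 | 6% | 6% | 6% |
| 0.1 | 0.10 | 0.10 | 5% | 17% | 21% |
| 0.2 | 0.20 | 0.20 | 5% | 55% | 71% |
| 0.3 | 0.30 | 0.30 | 4% | 89% | 97% |
| 0.5 | 0.46 | 0.46 | 6% | 100% | 100% |

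The simulation standard error at a 5% rate is √(0.05 × 0.95/1500) = 0.6 percentage points, so the baseline column agrees with the nominal 5%.

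**Step 6: does time ordering remove the artefact in this model?** Baseline: Cov(D0, A) = 0, so yes. Mid-way: Cov(D1, A2) = 0.6b, so the mid-way score is associated with later adherence through A1. Once A1 is in the model, A2 depends on nothing that D1 carries, and the coefficient of D1 is zero. The adjustment for adherence in weeks 1-8 is therefore essential.

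**The case against.** The strongest reply is that the protocol names the data and not the model. It does not say whether the four scores are averaged, entered jointly, matched in time or lagged. A separately published SAP is promised, and the form of a secondary regression is commonly left to it. This stands in part. A reader might infer that the protocol prescribes regressing adherence on a four-point average; it does not, and a lagged model is not excluded. What remains is that the protocol positively states that all time points are used, for a directional question, with no ordering. A SAP with ordered models would have to narrow that sentence.

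Second, question 5 also concerns physical activity maintenance. A reader might infer that the whole analysis is out of order. For activity after week 16, the baseline, mid-way and completion scores do come first, so using several time points is reasonable. The criticism is confined mainly to adherence.

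Third, the reverse effects are assumed. A reader might infer that the analysis would report false drivers. The documents support only that it could: at a reverse effect of zero nothing goes wrong, and nothing in the protocol fixes the size. Nor is one uniform effect across instruments supported. HTQ, for instance, measures a general tendency to rely on habits and may move little.

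Fourth, this is an observational secondary question, supplemented by exit interviews on reasons for engagement. That is right, and the randomised comparisons do not depend on it.

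**Conclusion.** The concern holds for the adherence part of questions 5 and 6. The stated data include two scores taken after the adherence period and one taken half-way through it, with no ordering, while the result is to be read as an effect or influence on adherence. If exercising changes the scores, reverse influence could be reported as an effect of the determinant.

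The size is illustrative. With no true effect, score stability of 0.6, n = 104 and reverse effects of 0.1 to 0.3 SD, the four-point average gives false-positive rates of about 17% to 89%, against about 5% for the baseline score. The conclusion on time order rests on the protocol's own schedule and not on those assumptions.

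It does not extend to the primary outcome, and it is much weaker for maintenance. There the difficulty is a different one: the timing table marks no exercise measure after week 16.

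**What to change.** In Section 9, for the adherence part of question 5, replace the use of all time points with time-ordered models in the SMART arm:

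- baseline determinants predicting adherence in weeks 1-16;
- mid-way determinants predicting adherence in weeks 9-16, adjusted for adherence in weeks 1-8.

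Apply the same ordering to PANAS in question 6. Report associations of completion and 12-month scores with adherence as descriptive only.

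For maintenance, use only determinants measured before the maintenance outcome. Confirm first that exercise is measured after week 16. If it is not, this part cannot be run and should not be claimed, or a measure has to be added.

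Cost: for adherence, analysis wording only, because the baseline and mid-way scores are scheduled and SMART participants' exercise is recorded weekly. Fewer predictor time points enter the adherence models, so they will show somewhat less apparent explanatory power. For maintenance, there may be a cost in added data collection.
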